## CRITICAL REVIEW OF THE LITERATURE.

*Staphylococcus aureus* is one of the main microorganisms that cause disease in humans and one of the main causes of bloodstream infections (bacteremia) worldwide. *S. aureus* bacteremia causes significant morbidity and increases healthcare costs; complications are frequent and mortality ranges from 20-40%. As a result, the concept of "complicated bacteremia" has been introduced. Predictors of complicated bacteremia are the persistence of bacteremia after 2-3 days of active treatment, the appearance of secondary foci of infection or infection of prosthetic valves and other prosthetic implants, endocarditis and specific cutaneous/mucosal lesions. More specifically, persistent bacteremia is considered a good predictor of possible complications and is a criterion for prolongation of antimicrobial treatment for 4 weeks. At the present time, the identification of

patients who develop complicated bacteremia is performed during the initial follow-up of the patient, pending the results of control blood cultures and other indicated diagnostic tests such as echocardiography. However, early identification of patients at high risk of developing complicated bacteremia would be of great use in planning treatment, monitoring for complications and evaluating more aggressive therapeutic strategies in this subgroup of patients. Independently of this, the pathogenesis of persistent bacteremia, when not due to endocarditis or an undrained focus, is not well established.

The approach outlined in this research project proposal is based on the hypothesis that patients who develop *S. aureus* bacteremia could be categorized into a few clinical patterns (phenotypes) based on demographic characteristics, comorbidities, history, signs, symptoms, and laboratory tests at presentation. Such phenotypes, if they exist, could be indicative of different physiopathological mechanisms, as well as be associated with a better or worse prognosis. They could help to better identify patients with *S. aureus* bacteremia at higher risk of complications and those who are not, which could improve treatment strategies and patient follow-up, resulting in a reduction in mortality and complications associated with this type of infection. In addition, the analysis of possible genetic, immunological and pathophysiological mechanisms that would explain the clinical presentation of bacteremia according to the phenotypes identified would lead to the investigation of new treatment strategies. Consequently, our proposal for this Research Project also includes a study of phenotypes associated with a higher or lower risk of developing complications and mortality, and an analysis of their differences based on genetics, microbiology (presence of virulence genes), immunological and physiopathological factors such as endothelial dysfunction (early biomarkers of endothelial dysfunction) and cytokine dysregulation.

Given the particular characteristics of the pediatric population, a specific subanalysis of this population is also foreseen. The Andalusian pediatric infectology and immunopathology group will contribute to the project for this part of the project.

Presentation according to different clinical phenotypes has been described in different pathologies but never in *S. aureus* bacteremia. For example, one study identified clinical phenotypes among patients with sepsis (Seymour et al. JAMA 2019). Our group also recently identified three clinical phenotypes associated with prognosis in patients with COVID-19 requiring hospital admission (Gutierrez-Gutierrez et al, Lancet Infect Dis 2021). It is considered that this approach to the study of such a serious pathology could be of great utility for the clinical management of patients (both in the adult and pediatric populations) and its results of great interest to the medical and scientific community.

## METHODS:

### Design and justification.

This is an entirely observational study.

For the Primary Objective and Secondary Objectives 1 and 2: the ISAC cohort will be analyzed. This cohort is the result of an international study (11 hospitals in 5 countries) on bacteremia caused by *S. aureus* in which the Hospital Virgen Macarena participated (2,590 cases have been collected, and it is estimated that at least 1,800 meet the criteria for inclusion). Authorization to perform the analysis for the FEN-FENAUREUS project has been obtained from the rest of the participating centers.

For Secondary Objectives 3 and 4 a multicenter prospective cohort study will be performed. All patients who develop *S. aureus* bacteremia will be assigned a phenotype and followed for 6 months to evaluate differences in mortality and development of complicated bacteremia between phenotypes.

For Secondary Objective 5 a study of genetic (microorganism and patient), immunological, biochemical and microbiological variables will be performed in representative patients with different phenotypes; these patients will be selected from the prospective cohort at two centers (HUVV and HUVV).

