**Table S9. Features and outcomes of patients in the FEN-AUREUS external validation cohort and in the phenotypes obtained.**

| Factor                                                         | A phenotype
(n=283) | B phenotype
(n=573) | C phenotype
(n=329) | P value |
|----------------------------------------------------------------|------------------------|------------------------|------------------------|---------|
| Demographics                                            |                        |                        |                        |         |
| Female sex                                                     | 99 (35·0)              | 184 (32·1)             | 100 (30·4)             | 0·52    |
| Median age in years (IQR)                                      | 66 (56–77)             | 66 (55–76)             | 71 (57–79)             | 0·001   |
| Comorbidities                                           |                        |                        |                        |         |
| Myocardial Infarction                                          | 39 (13·8)              | 130 (22·7)             | 58 (17·6)              | 0·006   |
| Peripheral vascular disease                                    | 44 (15·5)              | 55 (9·6)               | 26 (7·9)               | 0·004   |
| Dementia                                                       | 21 (7·4)               | 17 (3·0)               | 40 (12·2)              | <0·001  |
| Chronic Lung Disease                                           | 27 (9·5)               | 66 (11·5)              | 51 (15·5)              | 0·05    |
| Tumour                                                         | 28 (9·9)               | 114 (19·9)             | 72 (21·9)              | <0·001  |
| Chronic renal disease                                          | 62 (21·9)              | 153 (26·7)             | 70 (21·3)              | 0·10    |
| Chronic liver disease                                          | No liver disease       | 246 (86·9)             | 483 (84·3)             | 0·03    |
|                                                                | Mild                   | 24 (8·5)               | 41 (7·2)               |         |
|                                                                | Moderate or severe     | 13 (4·6)               | 49 (8·6)               |         |

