## ABBREVIATIONS AND DEFINITIONS

MIC: Minimum inhibitory concentration

*S. aureus*: *Staphylococcus aureus*

IV: intravenous;

HU: University Hospital

HUVM: University Hospital Virgen Macarena

HUVV: University Hospital Virgen de Valme

Community presentation: Infection occurring in a patient who was not hospitalized during the previous week, or starts within 72 hours of a hospital admission (this definition includes community infections and non-nosocomial healthcare-related infections).

Adverse Event: Any adverse or unfavorable event that appears in a study participant, including any sign, symptom or disease, whether or not considered to be related to the drug administered.

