## 8. Design.

This is an entirely observational study.

Primary Objective and Secondary Objectives 1 and 2: The ISAC cohort will be analyzed. This cohort is the result of an international study (11 hospitals in 5 countries) on bacteremia caused by *S.aureus* (2,590 cases collected) in which the University Hospital Virgen Macarena participated. The other participating centers have granted authorization to carry out the analysis for the FEN-FENAUREUS project.

Secondary Objectives 3 and 4: This will be a multicenter prospective cohort study. Each patient who develops *S. aureus* bacteremia will be assigned a phenotype and will be followed for 6 months to evaluate differences in mortality and development of complicated bacteremia according to phenotype.

For Secondary Objective 5: This study of genetic (microorganism and the patient), immunological, biochemical and microbiological variables will be performed on representative patients, selected from the prospective cohort (two centers HUVM and HUVV), with the different phenotypes obtained.

Inclusion criteria: adults and children with clinically significant *S. aureus* bacteremia (i.e., associated with at least 2 of the classic criteria for systemic inflammatory response: fever, tachycardia, tachypnea, decreased level of consciousness, hypotension, leukocytosis/leukopenia, or organ failure).

For the study of genetic, immunological, biochemical and microbiological variables in representative patients, a predefined number of patients with each of the phenotypes assigned by the probabilistic model will be randomly selected from the prospective cohort (at the HUV and HUVV).

Exclusion criteria: Non-clinically significant bacteremia; lack of follow-up blood cultures at 48-72 hours; patients who died in the first 48 hours; subsequent episodes in the same patient.

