### Secondary Objectives

- 1 To evaluate the reproducibility of the clinical phenotypes and their correlation with mortality (30 days and 6 months).
- 2 To derive and validate a simplified probabilistic model of clinical phenotype assignment.
- 3 External validation of the simplified probabilistic model of clinical phenotype assignment in a prospective cohort and determination of associations with mortality and the development of complicated bacteremia within 6 months.
- 4 To apply microbiological (clonality testing, genome sequencing), biochemical and immunological techniques to elucidate the pathophysiological and genetic mechanisms underlying the phenotypes.

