## **6. Data collection methods (prospective cohort).**

Data will be collected by prospectively obtaining information from DIRAYA of SAB episodes detected by the microbiology service at each of the participating Andalusian centers. Access to the electronic database, as well as prospective data collection to complete the electronic database, will be direct, remote, and carried out centrally by the HUVIM investigation team in conjunction with the local teams at each center. Patients will also be followed up for 6 months afterwards by center investigators.

Data will be collected in an eDCN (electronic data collection notebook) developed for the purpose:

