#### Microbiological studies:

**At all participating centers:** standard microbiological methods will be used, following SEIMC recommendations for the diagnosis of bacteremia (<http://www.seimc.org/documentos/protocolos/microbiologia>). For sensitivity testing, EUCAST guidelines will be followed.

**Studies to meet Objective 5 (100 isolates selected at HUVM and HUVV):** 1. Identification: Isolates will be identified by MALDI-TOF.

2. Sensitivity testing: The sensitivity of the 100 *S.aureus* isolates to the following antimicrobials will be tested by broth microdilution: penicillin, amoxicillin/clavulanic acid, oxacillin, gentamicin, tobramycin, amikacin, ciprofloxacin, levofloxacin, erythromycin, clindamycin, tetracycline, trimethoprim/sulfamethoxazole, linezolid, teicoplanin, vancomycin and daptomycin, following the EUCAST methodology.

3. Mass sequencing: Extraction of DNA from isolates will be performed using a Qiacube automatic extractor (Qiagen). The highly sensitive Qubit system (Thermo Fisher Scientific) will be used for fluorimetric quantification of extracted DNA. Enzymatic fragmentation of the DNA, addition of adapters and indexes, PCR amplification and subsequent clean-up, and library normalization will be performed according to the manufacturer's instructions (Nextera DNA Flex library prep kits [Illumina]). Library quality will be checked on the

Agilent 2100 Bioanalyzer system using a high-sensitivity chip. Library mixing and sequencing will be performed on a MiSeq sequencer (Illumina), using the Illumina MiSeq v3 reagent kit (600 cycles and 2x300 paired-end reads). Reads will be quality-filtered and assembled with CLC Genomic Workbench v10 (Qiagen) software. The RAST server will be used for gene annotation. FastQ files generated for each sample will be used for genotyping and identifying genes of interest (ResFinder and VirulenceFinder of the Center for Genomic Epidemiology CGE], <http://www.genomicepidemiology.org/>). These databases will also be used to establish clonal relatedness between strains using multilocus sequence typing (MLST finder).

**OTHER METHODS** (100 patients sorted by different phenotypes, from HUVm and HUVV):

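### HUVM supplies patients to both the ISAC derivation cohort and the prospective cohort labelled external validation, so the claim of transport to new hospitals should rest on a repeat without ISAC-contributing centres

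*Combined protocol and SAP*

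**What the plan says.** - **Derivation.** Protocol summary item 8 (Design) and Methods (Design and justification) base the phenotypes and the assignment model on ISAC, with 11 hospitals in 5 countries. Item 8 describes it as a study "in which the University Hospital Virgen Macarena participated", and Methods says "in which the Hospital Virgen Macarena participated". The abbreviations list gives "HUVM: University Hospital Virgen Macarena".
- **Prospective cohort.** The substudy patients are "selected from the prospective cohort (two centers HUVM and HUVV", and the microbiology section refers to "100 isolates selected at HUVM and HUVV". HUVM therefore enrols prospective patients.
- **Label.** The third secondary objective is "External validation of the simplified probabilistic model of clinical phenotype assignment in a prospective cohort". The appendix keeps the term: Table S9 is titled "Features and outcomes of patients in the FEN-AUREUS external validation cohort and in the phenotypes obtained", and Table S11 and Figure S3 report mortality in that cohort.
- **Analysis.** Data analysis (section 8, which numbers this Objective 4) assigns a phenotype to each prospective patient and compares outcomes between phenotypes. It has no stratum, exclusion or adjustment for centre. Section 10 (Limitations) does not mention the overlap.

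**The concern.** External validation asks whether a model built in some hospitals works in others. For patients from a hospital that helped to build the model, the question is narrower: does it still work there later?

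The distinction matters for these models because several strong predictors can depend on local epidemiology or work-up. In Table S6, MRSA carries adjusted odds ratios of 3.96, 12.2 and 5.69 in phenotypes A, B and C. In phenotype C, nosocomial acquisition carries 11.59 and a focus not established carries 5.21. The cut-offs of 0.19, 0.10 and 0.52 were also set in ISAC. A result that mixes a derivation hospital with new ones does not by itself show how the models and cut-offs behave in hospitals that played no part in setting them.

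**Working it through.** **1. Is it the same hospital?** The abbreviations list equates HUVM with Virgen Macarena. Design places Virgen Macarena in ISAC and HUVM in the prospective cohort. Some sections print the abbreviation differently: Methods prints the Valme abbreviation twice, and Data collection prints HUVIM. The design item of the summary and the microbiology section make the intended pair clear.

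**2. Does the derivation split hold HUVM out?** No. Data analysis takes a random two-thirds of ISAC patients for derivation and one-third for internal validation. The split is by patient, so no hospital is reserved.

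**3. Is the check temporal for HUVM?** Yes. Methods describes the ISAC cases as already collected, and the schedule gives prospective inclusion as June 2022 to June 2024.

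**4. How many patients?** The plan's figure is 1,000 cases from 14 centres. It is a recruitment estimate without a formula, so there is nothing to reproduce. Table S9 gives 283 + 573 + 329 = 1,185. HUVM's share s is not stated. I assume an equal share, 1/14, with a range of 5% to 20%.

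| s (assumed) | HUVM of 1,000 | HUVM of 1,185 | Remaining of 1,185 | Log-scale CI width × 1/√(1 − s) |
|---|---|---|---|---|
| 5% | 50 | 59 | 1,126 | 1.03 |
| 1/14 | 71 | 85 | 1,100 | 1.04 |
| 20% | 200 | 237 | 948 | 1.12 |

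**5. What would exclusion cost in precision?** The inputs are the Table S11 hazard ratios for sub-phenotype 2. The log-scale standard error is (ln upper − ln lower)/(2 × 1.96). For A this is (ln 3.29 − ln 1.25)/3.92 = 0.247; for B it is 0.248 and for C 0.259. Dividing by √(1 − s), with point estimates unchanged and information proportional to patients, gives:

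| Phenotype | Reported | s = 1/14 | s = 20% |
|---|---|---|---|
| A | 2.02 (1.25–3.29) | 1.22–3.34 | 1.18–3.47 |
| B | 2.11 (1.30–3.44) | 1.27–3.50 | 1.22–3.64 |
| C | 2.44 (1.47–4.06) | 1.44–4.13 | 1.38–4.31 |

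All the intervals still exclude 1 under these assumptions.

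**6. Could HUVM be modelled alone?** At 1/14 the standard error for A becomes 0.247 × √14 = 0.924, giving an interval of about 0.33 to 12.35. That is not informative.

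**7. How far could HUVM move the pooled estimate?** The documents give no HUVM-specific result. Purely as an illustration, suppose the hazard ratio were 3.0 at HUVM and 2.0 elsewhere. The pooled value would be exp(s·ln 3 + (1 − s)·ln 2). At 1/14 that is 2.06, a shift of ln(1.5)/14 = 0.029, or 0.12 of the phenotype A standard error. At 20% it is 2.17, a shift of 0.2 × ln(1.5) = 0.081, or 0.33 of that standard error.

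**The case against.** The strongest reply is that this is mostly a matter of labelling. Only one of 14 prospective centres is shown to overlap, and HUVM is only one of 11 ISAC hospitals. The plan applies an assignment model built on ISAC to patients recruited later.

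Nor is the prospective cohort a near-copy of ISAC. Phenotypes A/B/C make up about 22/27/52% of ISAC (458, 573 and 1,097 of 2,128) and 24/48/28% of FEN-AUREUS. MRSA is 374/2,128 = 17.6% against 117/1,185 = 9.9%.

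The appendix also reports a second external cohort, INSTINCT (n = 1,217), with sub-phenotype 2 hazard ratios of 1.93, 3.40 and 3.04. The cohort with the known overlap does not show systematically stronger associations. That comparison is loose: Table S11 also adjusts for an infectious-disease team visit, and the documents do not say whether INSTINCT hospitals were in ISAC.

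Much of this stands, and it rules out several stronger readings:

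- **The reported associations are inflated.** A reader might infer this, but no HUVM-specific result is given, and any contrast between HUVM and the other centres is assumed.
- **Central data collection makes HUVM a special case.** The protocol says this work is "carried out centrally by the HUVIM investigation team in conjunction with the local teams at each center". It applies to every prospective centre, and excluding HUVM patients would not remove it.
- **The same patients are in both cohorts.** The documents show overlap of hospital, not of patients.
- **The subset should replace the pooled result.** The overlap alone does not require that.

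The reply does not remove the gap itself. The documents use the external label without qualification, and the planned analysis gives no result confined to hospitals new to the model.

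**Conclusion.** The overlap is established from the documents' own text: HUVM is in the derivation cohort and in the cohort labelled external, and nothing separates the two roles. For HUVM patients the validation is temporal.

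The size is an assumption: about 85 of 1,185 at an equal share, and 59 to 237 at 5% to 20%. The direction and amount of any optimism are unknown. With one centre of 14 shown to overlap, the effect is probably modest. The documents do not support a conclusion that the validation fails or that the hazard ratios are overstated. Whether other prospective centres were ISAC hospitals cannot be told from the text available, so HUVM is the minimum overlap.

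This is a worthwhile, inexpensive improvement to the analysis, not a fault that undermines the main result.

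**What to change.** In Data analysis (section 8, prospective cohort):

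1. Keep the pooled prospective analysis.
2. Add a prespecified repeat of the phenotype distribution, model performance and mortality associations that excludes HUVM and any other prospective centre that contributed to ISAC. Rest any statement about transport to new hospitals on this result.
3. Report the number of HUVM patients, and of patients from any other overlapping centre. Show the HUVM patients descriptively as temporal validation, without a separate HUVM model.
4. List the overlap in section 10 (Limitations).

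The exclusion rule depends only on ISAC membership, not on outcomes. Since the appendix already reports FEN-AUREUS outcomes, the text should say when the rule was added.

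**Cost.** One repeat on data already held. Centre should be identifiable, because Data management gives each centre its own access key. The log-scale interval widens by about 4% at a 1/14 share and about 12% at 20%, and by more if further centres prove to overlap.

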### 2. Study population.

ISAC and prospective cohorts: Criteria for inclusion: adults and children (prospective cohort only) with clinically significant *S. aureus* bacteremia (i.e., associated with at least 2 classic criteria for systemic inflammatory response: fever, tachycardia, tachypnea, decreased level of consciousness, hypotension, leukocytosis/leukopenia, or organ failure).

For the study of genetic, immunological, biochemical and microbiological variables in representative patients: a predetermined number of patients belonging to each phenotype assigned by the probabilistic model will be randomly selected from the prospective cohort (HUVV and HUVV centers).

Exclusion criteria: non-clinically significant bacteremia; lack of follow-up blood cultures at 48-72 hours; patients who died in the first 48 hours; subsequent episodes in the same patient.

### 3. Source of information.

The source of information for the retrospective cohort will be the ISAC database. For the prospective cohort, the clinical history collected during follow-up visits of the patients in that cohort will be used.

### 4. Operational definitions of outcome, exposure and other variables.

- Outcome variables:
  - Primary outcome variable: all-cause mortality at day 30;

Secondary outcome variable: all-cause mortality at month 6 (measured as time-to-death, prospective cohort only). Persistent bacteremia (positive blood culture 2-3 days after initiation of appropriate targeted therapy). Complicated bacteremia (considered as presence of endocarditis, secondary foci, recurrence within 6 months). Hospital stay.

- 
- 

Explanatory: age, sex, service, type of acquisition (community-acquired, healthcare-related, nosocomial [Friedman criteria]; types of relationship with previous care), underlying diseases (diabetes, chronic lung disease, chronic renal insufficiency, chronic liver disease, immunosuppressive disorders, cancer, other), severity of underlying disease (Charlson index, McCabe classification), Barthel index, neutropenia, parenteral drug use, immunosuppressive treatment, recent invasive procedures (dialysis, catheter and vascular type, urinary catheter, mechanical ventilation, endoscopy, vascular procedures, surgery, percutaneous puncture), antibiotic therapy in the previous month, antibiotic susceptibility of *S. aureus*, Pitt and SOFA score on day 0 (blood cultures performed), sepsis or septic shock (Singer et al. JAMA 2016 for adults and Dellinger et al, Intensive Care Medicine 2013//Mathias et al, Curr Opin Pediatr 2016 for pediatric patients), acute kidney injury, empiric and targeted antibiotic therapy (drug, dose, route, day of onset and termination, reason for termination), source of bacteremia (clinical and microbiological criteria), management of source of infection (removal of catheter or other device, drainage), supportive care, echocardiographic data, if performed (transthoracic/transesophageal), CBC and basic blood chemistry at 0.

Exposure variables: Type of phenotype

- 

